### Study variables and data collection

Data will be collected according to the study timeline depicted in Figure 4. Baseline sociodemographic characteristics of EPs and participants, including age, gender, marital status, family support, educational level, and employment situation, will be collected during the recruitment visit. Disease variables, including, among others, date of diagnosis, type of MS, MS treatment, and disability, will be collected from the clinical records before the intervention (Week 1) and after the intervention (Week 9 and at 6 and 12 months after the end of the intervention). Variables related to the use of healthcare services include the number of visits to the MS unit (both scheduled routine follow-up visits and unscheduled visits), primary care visits, and A&E department visits during 1 year before and after the intervention, and will be collected prior to the intervention (Week 1) and after the intervention (Month 12), respectively, by the research team using a questionnaire. This information is routinely registered during visits to clinics and healthcare consultations. It is made available by the health registry of the region to the healthcare institutions after institutional authorization from the Ethics Committee of each center. Before the study starts, all the healthcare professionals involved will receive an update session led by the study’s PI regarding data entry to ensure uniform data collection (18).

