### Selection of participants and EPs

Patients with a diagnosis of MS treated in the participating MS units will be eligible to participate as participants or EPs in the deployment of the EPPC-MS. All members of the MS multidisciplinary teams will identify participant and EP candidates according to their criteria based on their MS-related knowledge and ability for self-care and self-management, and will invite them to participate. The teams coordinate the process of selection and assessment of participants’ inclusion criteria, including a visit with a trained neuropsychologist to administer the Brief International Cognitive Assessment for Multiple Sclerosis (BICAMS) (15) and Hospital Anxiety and Depression Scales (HADS) (16). Furthermore, the teams initiate and coordinate all the steps for the selection of EPs among pre-selected candidates. A nurse [i.e., the study’s principal investigator (PI)] will coordinate and provide support for these processes to the participating MS units, and will monitor the process to ensure protocol compliance.

Eligible participants must meet the following inclusion criteria: (1) be ≥18 years old; (2) have reported the need for support for disease self-management or to improve MS-related knowledge; (3) confirm availability to attend at least 80% of the sessions; (4) sign an informed consent. Patients meeting any of the following exclusion criteria will not be eligible: (1) be unable to speak or write in Spanish or Catalan; (2) have aphasia or an auditory disorder preventing them from interacting with the group; (3) have a severe cognitive impairment, defined as a score of 1.5-fold the standard deviation below the population mean in one of the three subtests of the Spanish version of the BICAMS (15); (4) have severe emotional impairment, defined as a score above 11/21 on any of the two Hospital Anxiety and Depression Scale (HADS) subscales (anxiety and depression) (16); and (5) have any psychopathological comorbidity or mental disorder diagnosis that may restrict their interaction with the group.

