### Recruitment

Participants: follow-up of people with MS involves therapeutic support by the multidisciplinary team during clinical visits at the unit facilities (i.e., regular follow-up visits), the day care clinic, or through non-scheduled consultations for any reason (i.e., needing additional care due to treatment secondary effects or disease symptoms, information, and support). After completing a routine follow-up visit by a healthcare professional, people with MS self-reporting the need for support for disease management or the need to improve MS-related knowledge will be invited to participate in the study. To ensure that the target sample size is reached, healthcare professionals, members of the MS multidisciplinary teams may actively identify candidates by asking people with MS about their need for additional support and information for disease management. People with MS initially willing to participate will be referred to the study coordinator at each participating center to receive complete information about the study.

Neuropsychologists within the MS multidisciplinary teams will assess the inclusion and exclusion criteria of participant candidates. To assess severe cognitive and emotional impairment (exclusion criteria), a trained and experienced staff in assessing cognitive and emotional impairment will screen participant candidates using the BICAMS (15) and HADS (16) instruments. These tests are part of the routine neurorehabilitation screening procedure, but may be administered to other participant candidates outside the routine screening that require a specific consent. Before the study starts, a senior neuropsychologist will lead an update session for all neuropsychologists of the participant centers to ensure uniformity of data collection (18). Eligible candidates will receive the patient information sheet and be asked to sign a written informed consent before assessing the selection criteria, such as cognitive and emotional impairment (when required). The participant timeline summarizes the recruitment process (Figure 3).

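### The before-year count of MS-unit visits can include recruitment and study-specific screening contacts that have no counterpart in the after year

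*Protocol article*

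**What the plan says.** Use of healthcare services is a secondary outcome. Under Study variables and data collection, the protocol article defines it through "the number of visits to the MS unit (both scheduled routine follow-up visits and unscheduled visits", followed by "primary care visits, and A&E department visits during 1 year before and after the intervention". The before count is collected at Week 1 and the after count at Month 12. The research team uses a questionnaire for this, and the article adds: "This information is routinely registered during visits to clinics and healthcare consultations".

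Entry to the study passes through the same units:

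- **Invitation.** Recruitment gives the main route: "After completing a routine follow-up visit by a healthcare professional, people with MS self-reporting the need for support" are invited. To reach the target, staff "may actively identify candidates by asking people with MS about their need for additional support"; no type of visit is fixed for this second route.
- **Screening.** Selection of participants and EPs describes the process as "including a visit with a trained neuropsychologist to administer the Brief International Cognitive Assessment" and HADS. Limitations shows that candidates attend the units for this. The Figure 2 note and Recruitment say that the tests are already routine for some candidates and are done outside routine screening for others.
- **Baseline data.** Sociodemographic data "will be collected during the recruitment visit", which may or may not be a separate contact.

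After the intervention, the study contacts described are online questionnaires and group follow-up sessions at 6 and 12 months. Programme sessions are held remotely.

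**The concern.** A before/after count is fair only if both windows would hold the same number of visits when nothing changes. Here the before window ends at the intervention, so any contact that exists because of recruitment or eligibility testing falls on that side alone. Nothing in the article says that such contacts are left out.

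The direction matters. The Introduction and the Discussion both expect such programmes to reduce use of services, and an excess in the before year produces that result without any effect. In a single-group design, no comparison arm would show the same artefact. A fall that comes from the counting rule could then be reported as a benefit.

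**Working it through.** **Figures the article gives.** 6 teams × 2 groups × 12 people = 144. The expected minimum retained is 12 × 8 = 96 to 12 × 10 = 120. These are deployment numbers. The article gives no visit rate, effect size or power for healthcare use, so the rates below are assumptions.

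**Do these contacts fall inside the before year?** The interval from recruitment to Week 1 is not stated. There are four consecutive phases of about 3 months each. A Phase 4 participant recruited just before Phase 1 would start about 3 × 3 = 9 months later, still within 12 months. It is therefore likely, though not fixed, that they do.

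**Recruiting visit on a regular schedule.** Place that visit 1, 3 or 5 months before Week 1. Count 12 months back from Week 1, and 12 months forward from 2 months after Week 1. Before and after counts are 4 and 4 for three-monthly visits, 2 and 2 for six-monthly, and 1 and 1 for yearly. The excess is zero.

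**Where an excess arises.** A screening visit made only for the study adds one visit to the before year. Recruitment at an unscheduled or irregular contact can also add one: if visits come at random times, choosing a person at a visit adds that visit to the count. Let e be the mean number of extra visits per participant and L the true yearly rate, equal in both years.

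Apparent fall = e / (L + e)

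| Participants with one extra visit | L = 2 | L = 4 | L = 6 |
|---|---|---|---|
| 25% (e = 0.25) | 11% | 6% | 4% |
| 50% (e = 0.5) | 20% | 11% | 8% |
| 100% (e = 1) | 33% | 20% | 14% |

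**Would it be significant?** With Poisson counts, z = e / √(2L/n). At n = 120:

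- e = 0.5: 0.5/√(4/120) = 2.74, 0.5/√(8/120) = 1.94 and 0.5/√(12/120) = 1.58 for L = 2, 4 and 6. With twofold overdispersion (divide by √2) these become 1.94, 1.37 and 1.12.
- e = 0.25: half of the first set, that is 1.37, 0.97 and 0.79.

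A simulation of the planned paired Wilcoxon test (two-sided 5%, Poisson visits, no true effect, 600 runs per setting) gave these shares of runs with a falsely significant fall. Ranges run from L = 6 to L = 2.

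| Participants with one extra visit | n = 96 | n = 144 |
|---|---|---|
| none | 2–3% | 3% |
| 25% | 9–23% | 13–28% |
| 50% | 28–64% | 38–83% |

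The risk of a false fall is raised well above nominal, but in most of these settings a significant result is not assured.

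**The case against.** The strongest reply is that the article never says a screening visit is counted. A neuropsychologist's eligibility assessment is neither clearly a scheduled follow-up nor an unscheduled visit. The coding rule may sit in the full protocol or in the data-entry briefing that staff receive before the study. This stands: the text allows the extra visits in the count but does not show that they are there.

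It also stands that the main recruitment route is a routine visit. The words "through non-scheduled consultations for any reason" come from a general description of MS follow-up care and do not define how patients are recruited. A reader might infer that everyone enters at a moment of high use and that later visits must fall through regression to the mean. Entry depends on a reported need for support or knowledge, not on a visit count, so the documents do not establish that.

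Finally, this is one component of one secondary outcome. The primary outcome is deployment, and Limitations disclaims causal aims. That limits the weight of the point. However, Objectives lists healthcare use among the effectiveness questions, and a counting artefact would misdescribe even a plain before/after change.

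The reply does not remove the anchoring of the window. That is a stated rule, not an omitted detail, and it places entry contacts on one side only.

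**Conclusion.** The MS-unit visit count is open to an asymmetry that favours an apparent fall. The possible sources are study-specific screening visits and recruitment at unscheduled or irregular contacts, in shares that the article does not give. With assumed rates of 2 to 6 visits a year and one extra visit in 25–50% of participants, the apparent fall is about 4–20%, which may or may not be significant.

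Two stronger readings are tempting. The first is that a fall is built in for everyone: one extra visit per person would give 33%, 20% or 14%, with z of 5.5, 3.9 or 3.2 at n = 120. The documents do not support this, because the main recruiting visit is routine and screening is study-generated only for some. The second is that healthcare use as a whole is biased. Primary care and A&E counts are not affected by study contacts.

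**What to change.** 1. State that recruitment, eligibility and other study-generated contacts are not counted as MS-unit visits in either window.
2. End the 12-month before window on the day before the recruiting contact, or show this as a sensitivity analysis. Where the window still ends at Week 1, keep a routine recruiting visit in the count and leave out only the study-generated contacts. Dropping a routine visit from the unmoved window would leave a six-monthly attender with 1 visit before against 2 after, which reverses the bias.
3. Report scheduled and unscheduled MS-unit visits separately. The definition already distinguishes them.

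The visits are already registered, so the cost is a counting rule in the data-entry instructions and the date of the recruiting contact. The downsides are a slightly lower baseline count and a short uncounted gap before Week 1.

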**Figure 4 fig4:**
[figure not shown]
Assessments and data collection timeline. BICAMS, Brief International Cognitive Assessment for Multiple Sclerosis; EP, expert patient; FSS, Fatigue Severity Scale; HADS, Hospital Anxiety and Depression Scale; MSQoL-54; Multiple Sclerosis Quality of Life-54 items; PAM-13, patient activation measure; PRT, participants; RT, research team.

Patient-reported outcomes (PROs) and PREMs evaluating the impact of the intervention (secondary outcomes) will be assessed using specific instruments (i.e., questionnaires) according to the study timeline (Figure 4). Except for participants and EP experience with the program, which will be evaluated after the intervention, questionnaires will be self-administered prior to the intervention (Weeks 1–3) and after the intervention (Week 9, Month 6, and Month12). Pre-intervention questionnaires will be distributed within the first 3 weeks considering the contents of each session. Hence, questionnaires assessing fatigue and lifestyle will be administered in session 2 (Week 2) and the corresponding contents will be presented in sessions 3 and 5, respectively. The Research Electronic Data Capture (REDCap) platform will automatically send the questionnaires and instructions for completion, and participants will complete them online on the platform’s site. The platform automatically resends the questionnaires weekly during three consecutive weeks in case answers are not received. Moreover, it allows real-time monitoring of the questionnaires received and the PI may resend the questionnaires manually and contact participants to solve any issues regarding questionnaire completion on the platform’s site.

The study’s PI, a nurse, will maintain a field notebook to record the basic information for each session, including participants, the session’s contents, the group, and the MS reference unit. The PI will additionally collect participants’ comments and questions related to the session’s topic and final comments regarding each session development. The EP will answer all questions collected as unanswered during each session in the next. Furthermore, the EP will clarify any inappropriate or inaccurate information shared during sessions in the next session, with the support of the research team.

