**Methods:**

Pre-post intervention multicenter clinical study involving 12 groups of 12 participants: six groups including relapsing and six groups including progressive MS patients, with 144 participants from 7 MS reference units from all over Catalonia, organized in six teams. The intervention will consist of nine telematic learning peer-led sessions (one weekly session). The expert patient (EP) leading the sessions will be an individual with MS with disease-related knowledge, who will be further trained by nurses to lead the sessions. Study variables will be measured before and immediately after the intervention and 6 and 12 months after the end of the sessions and will include: QoL, emotional impact, activation of the person, MS-related knowledge, fatigue, habits and lifestyles, health services use, and program-related experience. Baseline characteristics considered will be sociodemographic data, date of MS diagnosis and type, family history, and treatment characteristics. Variables related to disease follow-up will be new relapses and characteristics and changes in the ongoing treatment. The number of sessions attended will also be collected. Study variables will be analyzed using a pre-post comparison.

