### Intervention

The intervention aims to reinforce positive knowledge concisely using plain language that all participants can understand. Throughout nine 90-min sessions (one per week) led by an EP, participants in the group will share their knowledge and experiences on all aspects of MS and its self-management. The organization of session and its contents are summarized in Table 1.

**Table 1 tab1:** Expert Patient Program Catalonia-Multiple Sclerosis (EPPC-MS): sessions and contents.

Session	Content description
1. Introduction	Presentation of group members, program objectives, session contents, session development, and questionnaires
2. The disease	What is multiple sclerosis? Concept, causes, types of MS, and diagnosis
3. Signs and symptoms	Relapses (relapsing MS), progression (progressive MS), and fatigue
4. Treatment	Existing treatment, future treatments, treatments during pregnancy, and alternative therapies
5. Health promotion	Healthy lifestyles: nutritional facts, activity and exercise, tobacco, vitamin D and sun exposure, and obesity
6. Taboo subjects	Urinary and fecal incontinence, sexuality, and sexual dysfunction
7. Emotional impact and relationships	Coping with the disease, work and family relationships, and available resources for emotional support
8. Social environment and quality of life	Rehabilitation and physical aspects, social resources, and benefits
9. Program finalization	Wrap-up session

The study’s PI is a nurse specialized in MS and will train the EPs and support them throughout the intervention, together with professionals in each of the participating units. Before starting the intervention, the study’s PI will train the EPs in a presentation of all the learning materials and contents of each session. Furthermore, using role-playing activities, the nurse PI will ask example questions related to the contents of each session to the EPs to be answered jointly. The training and activities aim to expand the EPs’ knowledge of the sessions’ contents and gain confidence to lead and answer the questions.

Throughout the intervention, a professional nurse in the MS team and the EP will meet before each session to prepare the contents and solve any doubts from the previous sessions. In all sessions, two nurses, on from the participating team and one member of the EPPC panel of directors, will act as an observers, provide help and support to the EP if needed, and assess each session jointly with the EP at the end.

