Sessions are divided into two blocks: a first block with a theoretical introduction to focus on the day’s topic, conducted by the EP (30 min), and a practical block (60 min). A previous pivotal study characterized the topics addressed in the sessions (12). After the first block introducing the topic, the EP will encourage interaction, facilitating the communication of doubts, questions, or experiences related to the contents, which will be solved or answered by participants or collectively through discussion within the group (practical block). This intervention strategy with an EP leading the session and the participation of all the group members aims to empower them to gain control over their health situation. The knowledge acquired will come from the information provided by the EP and the knowledge resulting from the life experiences regarding MS of all the participants involved in the intervention.

Participants will complete questionnaires according to the study schedule (prior and immediately after the intervention, and at the evaluation periods 6 and 12 months after the end of the intervention) to assess the secondary outcomes. The completed questionnaires will be collected at post-intervention sessions (at 6 and 12 months), allowing participants to clarify concepts and expose doubts regarding the contents of the previous nine sessions.

To ensure adherence, the platform will send reminders before each session and, if necessary, sessions will be rescheduled.

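### Baseline questionnaires labelled pre-intervention are collected in Weeks 1–3 of the programme, and the reminder rule lets them be answered after the matching topic has been taught

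*Protocol article*

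**What the plan says.** The abstract states that "Study variables will be measured before and immediately after the intervention". The Intervention and Outcomes sections likewise describe scores obtained ahead of the programme and compared with later ones.

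The section on study variables and data collection sets the actual timing. There, "questionnaires will be self-administered prior to the intervention (Weeks 1–3) and after the intervention (Week 9, Month 6, and Month12". It adds that "Pre-intervention questionnaires will be distributed within the first 3 weeks considering the contents of each session". Two instruments are dated: "questionnaires assessing fatigue and lifestyle will be administered in session 2 (Week 2". Of the topics that these two forms measure, it says that "the corresponding contents will be presented in sessions 3 and 5, respectively". Table 1 confirms that session 3 covers "Relapses (relapsing MS), progression (progressive MS), and fatigue" and that session 5 covers healthy lifestyles.

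On non-response, "The platform automatically resends the questionnaires weekly during three consecutive weeks in case answers are not received". The principal investigator may also re-send forms by hand. No date is given after which a baseline form is closed or no longer counts as baseline.

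**The concern.** The effectiveness questionnaires are analysed as before-after contrasts in a single cohort. With no control arm, nothing else in the design can absorb a misplaced baseline. If a form is answered after part of the teaching, any gain already made is counted in the baseline and subtracted from the measured change.

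The lateness will also differ between people. Those who need reminders are not a random subset, so the baseline would mean something different for prompt and late responders. A pre-teaching score that was not collected cannot be recovered afterwards.

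**Working it through.** **Inputs.** Nine sessions, one per week (Intervention). Session 2 falls in Week 2 (data collection section), so session k is taken to fall in Week k. A form first sent in Week w is re-sent in Weeks w+1, w+2 and w+3. The plan gives no figure of its own on this point; its recruitment target (6 teams × 2 groups × 12 = 144) does not depend on it.

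**Step 1: is the window before the intervention?** Weeks 1–3 contain sessions 1–3, that is 3 of 9. The label does not fit the schedule.

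**Step 2: how late can an automatic reminder fall?** The last re-send is in Week w+3: 1+3 = 4, 2+3 = 5, 3+3 = 6. The last automatic prompts for baseline forms therefore fall in Weeks 4, 5 and 6 for forms sent in Weeks 1, 2 and 3.

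**Step 3: does each form stay ahead of its topic?**

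| Form | First sent | Re-sent | Topic taught | Result |
|---|---|---|---|---|
| Fatigue | Week 2 | Weeks 3, 4, 5 | Session 3 | Week 3 re-send is in the teaching week; Weeks 4 and 5 are after it |
| Lifestyle | Week 2 | Weeks 3, 4, 5 | Session 5 | Weeks 3 and 4 are ahead of it; Week 5 is in the teaching week |
| Knowledge | Not in the text; Week 1 is the earliest in the window | Weeks 2, 3, 4 at the earliest | Sessions 2–4: the disease, symptoms, treatment | Every re-send is in or after a week of relevant teaching |
| MSQoL-54, PAM-13 | Not in the text (Figure 4, not shown) | w+1 to w+3 | No single session | Staggering by topic gives no protection if answered after Week 1 |

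**Step 4: direction of the effect.** Let B be the score before teaching, g the gain already made when the baseline form is answered, and P the later score. The measured change is P − (B + g) = (P − B) − g. If early sessions help, g is in the direction of benefit and the change is understated. If g grows with the sessions attended, the loss is larger for late responders. Neither g nor the share of late responders is given, so no size follows.

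**Assumption on the calendar.** The Overall study design section gives an average duration of about 3 months, and sessions may be rescheduled. If sessions slip while the REDCap dates do not, some reminders would fall further ahead of their content. The text does not say whether the two move together.

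**The case against.** The case for the plan as written has real parts.

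- The primary outcome is deployment. Effectiveness is secondary, and the Limitations section disclaims causal aims. A late baseline mostly works against finding a benefit. This stands, and it lowers the severity.
- The staggering is deliberate, and prompt responders are largely protected. Session 1 is an introduction without disease teaching, so a form answered in Week 1 before or at that session is effectively clean. This stands. The fault lies in the label and in the late returns.
- For lifestyle, only the last of three re-sends reaches the teaching week. This stands; fatigue is the clearer failure.
- Closing dates could be an operational detail left to a fuller protocol. This does not answer the point, because the article itself fixes the window and the reminder rule, and together they defeat the stated safeguard.

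Several stronger readings are tempting, and the document does not support them:

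- *All effectiveness outcomes are biased.* Healthcare use compares visits in the year before and the year after, so form timing hardly matters. Satisfaction has no baseline. HADS is also measured at screening, before any session, although the plan does not name that score as the baseline.
- *A fixed share of the effect is lost.* That needs an assumed build-up of benefit across sessions, which the document does not give. Nor does its text name any form sent in Week 3, so the Week 6 reminder has no known instrument attached.
- *Persistence at Months 6 and 12 is overstated.* The plan says "The completed questionnaires will be collected at post-intervention sessions (at 6 and 12 months), allowing participants to clarify concepts and expose doubts". That does not say the forms are answered after the clarification, and the data collection section has them completed online.
- *People who leave by Week 3 have no baseline.* Distribution starts in Week 1, so they may have some forms; the text does not settle it.

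**Conclusion.** The concern holds for the secondary questionnaire outcomes and should be fixed. The document contradicts itself on when baseline is taken. Followed exactly, its reminder rule accepts fatigue baselines after fatigue has been taught, and knowledge baselines after disease teaching has begun. For lifestyle the overlap is confined to the week of session 5. For MSQoL-54 and PAM-13 the exposure depends on send dates in Figure 4, which is not shown.

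The likely direction is an understated pre-post change, greater in late responders. This assumes that early sessions move scores in the direction of benefit. The size cannot be derived from the document. The conclusion also rests on session k falling in Week k and on late forms being accepted as baseline, since no cut-off is stated. The primary outcome is untouched.

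**What to change.** 1. Send all baseline questionnaires in REDCap before session 1, with the weekly reminders finishing before it starts. If staggering is kept, close each form before its own content session and stop describing Weeks 1–3 as preceding the intervention.
2. Where late forms are accepted, flag them by REDCap completion timestamp and report a sensitivity analysis that excludes them. If groups have already run, this part can still be done.
3. Use the screening HADS as the pre-teaching baseline where the REDCap one is late. State that it also decided eligibility and may date from an earlier routine assessment, so it is not fully interchangeable with the REDCap score.

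The cost is a change of REDCap send and close dates and a sentence or two in the protocol. The downside is a heavier questionnaire load before session 1 and probably a few more missing baselines. The plan does not impute, so an ANCOVA would drop those participants from a sample expected to retain 96–120. A linear mixed model, which the plan also allows, can keep them if baseline is modelled as one of the repeated measurements.
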